### Primary and Secondary Outcomes

#### Primary Outcome

The primary outcome was the mRS score at 90 days in patients with ischemic stroke who received ET. The mRS measures the degree of disability after a stroke with a score ranging from 0 to 6 (0=no deficit; 1=minor deficit without limitations; 2=deficit with limitations; 3=dependence, but independent walking possible; 4=dependence, independent walking no longer possible; 5=being bedridden; and 6=death) [22-24]. The primary outcome was assessed by a structured telephone interview conducted by a central assessor blinded to group allocation.

#### Secondary Outcomes

Prespecified secondary outcomes were the dichotomization of the mRS (day 90) into scores of 0-2 and 3-6 and the time from emergency call to hospital admission.

### Control Variables

Control variables were age, sex, pre-mRS score, and severity of stroke (National Institutes of Health Stroke Scale) [25] at hospital admission.

### Data Collection

This study’s team asked each participating ECC to share their aLVO-query results with the research team along with time metrics. This study’s authors also collected deidentified case data from the 2 ECCs receiving endovascular treatment in a database. A study staff member blinded to group allocation requested the 7-point (0-6) mRS by telephone from patients with stroke receiving endovascular treatment or their guardians 90 days after stroke (unblinded treatment and blinded end point assessment). For the health economic evaluation, this study’s authors asked the medical controlling department of the University Medical Centre of Freiburg.

### Health Economic Evaluation

This study’s team will analyze the costs associated with hospitalization and the intervention for all the patients. Data will be provided by the medical controlling department of the University Medical Centre. This study’s authors will also perform a cost-effectiveness analysis, whereby the primary end point (mRS) is related to the total costs.

### Power Considerations

A power analysis showed that testing for the statistically significant superiority of the intervention over the control group required far more cases (N=664) than available in the target region during this study’s period. This study’s authors, therefore, conducted a controlled feasibility study to explore achievable effects and practicability under routine care conditions. This study’s team will explore the clinical significance of the intervention effects and refrain from testing for the statistical superiority of the intervention over the control group.

### Statistical Analysis

We will use a generalized linear mixed model following the basic model proposed by Hussey and Hughes [26], including the 6 districts as clusters. This study’s team will extend the model as proposed by Hemming et al [27] and Li et al [28] to control for the secular trend to avoid potential bias. We will therefore stratify the sample by the 2 stroke centers and add a fixed effect for the secular trend stratified by each of these 2 hospitals, taking into account the control variables. We will assume the same treatment effect in both strata but will exploratively test this assumption by extending the model with an interaction term.

As studies have shown that it is advantageous to examine the full-scale range of mRS—rather than dichotomizing it—this study’s authors will account for the ordinal scaling of the mRS [29].

We will conduct exploratory subgroup analyses for cases within and outside of the catchment areas of the 2 CSCs and consider the dichotomous mRS because a favorable clinical outcome is defined as mRS≤2 similar to Goyal et al [2]. In addition, the area under the curve for different mRS cutoff values will be calculated in an exploratory sensitivity analysis.

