**Figure 2 figure2:**
[figure not shown]
Stepped wedge, cluster trial design of the LESTOR study in 6 districts. LESTOR: Leitstellen-Basierte Erkennung von Schlaganfall-Patienten für eine Thrombektomie und daraufhin abgestimmte Optimierung der Rettungskette.

Each cluster includes 1 ECC. Ground emergency medical ambulances are nearly equally distributed across the districts. All 6 districts are supported by 3 air rescue facilities. Further, 6 PSCs and 2 CSCs provide stroke service. The research team sequentially assigns the clusters to the intervention at intervals of 2 to 3 months in an unblinded manner (Figure 2).

This study’s team implemented the multicomponent LESTOR approach simultaneously for each cluster’s ECC, EMS personnel, EPs, and stroke units. Since HEMS were involved in the intervention from the beginning, this study’s authors introduced the LESTOR approach to the 3 air rescue facilities before the implementation of the first cluster.

Each cluster passed through the following phases:

Phase 1 was the control phase (preintervention baseline phase, 3-15 months). During phase 1, ECCs carried out the emergency call and stroke dispatch by local standards: they used the FAST scale for stroke detection, followed by the immediate dispatch of EMS (with additional EP dispatch depending on local conditions). EMS personnel and EPs also used the FAST scale for stroke detection at the scene. The standard allocation for stroke patients was the nearest stroke unit (regardless of whether it is a PSC or CSC). Allocation to CSCs outside their catchment area was based on an individual decision by the EMS or EP to contact the CSC and requires CSC approval. If a helicopter was considered to be the most suitable means of transport on-site, a sequential additional request for the helicopter must be made.

Phase 2 was the implementation phase, when all the professionals involved in acute stroke patient care in a cluster participated in seminars (see above) paralleling the technical implementation of the aLVO query.

Phase 3 was the intervention phase (14-26 months), which follows the intervention’s implementation as described above.

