### Process Evaluation

The process evaluation will consist of semistructured, guideline-based individual telephone interviews conducted by trained researchers to assess the implementation process at 2 points in time (in the middle of and at the end of the intervention phase). This study’s authors will interview representatives of the ECC, EMS and HEMS personnel, EPs, and first responders. A study nurse will recruit lay first responders of patients receiving ET at the University Hospital of Freiburg to participate in interviews. Key topics for the interviews with medical professionals will be the feasibility of implementation, accessibility, acceptability, appropriateness, fidelity, penetration, and sustainability of the intervention. This study’s authors will ask lay first responders about the emergency and personal stress, and the instructions given during the emergency call. Further, 2 independent researchers will use Kuckartz’s [31] multistage qualitative content analysis to analyze transcribed data using MAXQDA (VERBI Software GmbH) software.

The results of the first interview round will provide input for a midintervention workshop for all participating medical professionals involved in this study. The workshop aims to discuss the experience and data gained to improve the intervention. The results of the second interview round may help to optimize the intervention for future implementations and projects.

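### The planned model has one constant on/off effect, yet a mid-phase workshop is meant to improve the intervention after the last district has crossed, so the estimate describes the pre-workshop intervention only

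*Protocol article*

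**What the plan says.** **Model (protocol article, Statistical Analysis).** A generalized linear mixed model is planned "following the basic model proposed by Hussey and Hughes [26", "including the 6 districts as clusters". The extension is there "to control for the secular trend to avoid potential bias": the plan will "add a fixed effect for the secular trend stratified by each of these 2 hospitals". Whether that trend is categorical or linear is not stated. On the treatment effect itself, the section says "We will assume the same treatment effect in both strata", to be checked by an exploratory interaction. Subgroups inside and outside the comprehensive stroke centers' catchment areas are also exploratory. No stated term lets the effect differ by time since a district went live.

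**Timing (Study Design).** The team "sequentially assigns the clusters to the intervention at intervals of 2 to 3 months". The control phase lasts 3 to 15 months. A training phase of unstated length follows, and then "Phase 3 was the intervention phase (14-26 months").

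**Planned change (Process Evaluation).** A first interview round in the middle of the intervention phase feeds a workshop for all participating professionals. "The workshop aims to discuss the experience and data gained to improve the intervention".

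**Use of the estimate (Power Considerations).** No superiority test is planned. The clinical significance of the effects will be explored instead.

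**The concern.** The plan sets out to change the intervention while it is running, but analyses it as one unchanging thing. In a stepped-wedge design the treatment effect is identified from months in which some districts are treated and others are not. A change that reaches every district after the last crossover has no concurrent control, and the model cannot tell it apart from a calendar trend.

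This matters because the size of the estimate is the main clinical result here. A reader would naturally take it as the average effect over the whole intervention phase, when it may describe only the first version of the strategy. The cost-effectiveness analysis relates the same endpoint to costs and inherits the ambiguity.

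**Working it through.** The article gives no effect size for the workshop, so there is no plan figure to reproduce. The check has three steps.

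**1. When the workshop falls.** From Study Design, 3 + 26 = 29 and 15 + 14 = 29 months. The first district therefore starts phase 3 at about month 3 and the last at about month 15. Mid-phase is 3 + 26/2 = 16 for the first district and 15 + 14/2 = 22 for the last. A workshop that follows mid-phase interviews thus comes when no control district is left. (Phase 2 is not visible in this sum; I assume it does not alter the order of events.)

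**2. What the model does with a workshop gain.** Assumed crossovers are months 3, 5, 8, 10, 13 and 15, which fit the 2-to-3-month steps.
- Intervention district-months: 26 + 24 + 21 + 19 + 16 + 14 = 120.
- From month 16 onward: 6 × 13 = 78. Before it: 120 − 78 = 42.
- Effect rising from 0.5 to 1.0 at month 16: true mean = (42 × 0.5 + 78 × 1.0)/120 = 99/120 = 0.825.
- Effect rising from 0.75 to 1.0: true mean = (42 × 0.75 + 78 × 1.0)/120 = 109.5/120 = 0.9125.

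After month 15 all six districts are treated. A common gain from month 16 has exactly the form of a shift in the later period effects, which fit it completely. The treatment coefficient is therefore the pre-workshop value: 0.50 (ratio 0.50/0.825 = 0.61) or 0.75 (ratio 0.75/0.9125 = 0.82). With categorical periods this holds for any intracluster correlation (ICC) and any split of districts between the hospitals. At month 22 the true mean would be (78 × 0.5 + 42 × 1.0)/120 = 0.675, and the estimate is still 0.50. A linear trend does not help: for the doubling at month 16 it returns about 0.47-0.48.

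**3. If the effect changes with time since go-live.** The expected value of the generalized least squares estimator, (X′V⁻¹X)⁻¹X′V⁻¹E[y], was computed on the same 6 × 29 grid. Assumptions: random district intercept, pooled monthly period effects, linear scale, 2.5 patients per district-month, ICC 0 to 0.10, full effect = 1.

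| Assumed effect curve | True mean | Constant-effect estimate |
|---|---|---|
| Constant | 1.00 | 1.00 |
| 3-month build-up | 0.925 | 0.67-0.74 |
| 6-month build-up | 0.85 | 0.41-0.55 |
| 12-month build-up | 0.70 | 0.11-0.31 |

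Stratifying by hospital does not remove the shortfall: at ICC 0.01 the 6-month ratio is 0.33-0.63, depending on the split. If the effect wanes from 1 to 0.5, the estimate is 1.16-1.32 times the true mean.

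Monthly exposure-time terms recover the 6- and 12-month build-ups (0.85 of 0.85; 0.70 of 0.70), with the standard error rising from 0.176 to 0.236 at ICC 0.01 and from 0.182 to 0.302 at ICC 0.05. With four coarser categories (0-3, 3-6, 6-12, >12 months) the standard error is about 25-60% larger, and recovery is partial: about 0.79-0.81 of 0.85 and 0.58-0.62 of 0.70, lower for unfavourable hospital splits. For the month-16 workshop with categorical periods, every version stays at 0.50.

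**The case against.** **Learning is not stated.** A reader might infer that the plan expects the effect to grow with exposure and that the estimate will therefore fall far below the truth. The article does not say so. Phase 2 trains staff before phase 3, the air rescue facilities were introduced to the approach before the first district, and the Results section reports integration into daily work before enrolment. The app and the refresher materials suggest continuing consolidation, but no more. The build-up curves are assumptions, and waning would reverse the bias. This objection stands: neither the direction nor the size of any exposure-time bias can be taken from the document.

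**The workshop is a design limit, not a modelling error.** Post-workshop gains have no concurrent control, so with categorical periods no treatment term recovers them. This also stands. It is why the remedy for the workshop is a statement of what is estimated.

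**Exposure-time terms are costly.** Reading N = 664 as a 1:1 two-sided 5% comparison without clustering (the article gives none of these), the detectable effect is 2(1.96 + 0.84)/√664 = 0.22 SD at 80% power and 2(1.96 + 1.28)/√664 = 0.25 SD at 90%. At effects of that size, the four-category average had a larger mean squared error than the constant-effect estimate in every 6- and 12-month build-up examined. That argues against replacing the primary model, not against a sensitivity analysis.

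**Such detail belongs in the analysis plan.** An unseen plan may well add these terms, and their absence alone would be no finding. What remains is that this article states a constant-effect model and, separately, an intention to change the intervention, without reconciling the two.

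**Conclusion.** The point holds in a limited form. On the stated phase lengths, and with categorical period effects, the estimate refers to the intervention before the workshop. That conclusion needs no assumption about the ICC, the outcome scale or the hospital split. It does need the workshop to fall after the last crossover and to reach all districts together. How far the estimate departs from the average over the whole phase depends on how much the workshop changes the effect, which is unknown: a ratio of 0.61 if it doubles the effect, 0.82 if it raises it by a third, 1 if it changes nothing. A workshop before month 15 would leave some control districts for comparison.

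The possible bias from build-up or waning is a real sensitivity of the model, but its size and sign rest on assumed curves, ICC and a linear scale.

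A reader might also infer that a useful strategy would be declared ineffective. The article contains no such decision rule: it describes a feasibility study and says the sample is likely too small to show superiority. The consequence is a mislabelled effect size, which is cheap to correct.

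**What to change.** 1. Keep the planned model as primary.
2. State that its estimate refers to the intervention before the workshop, because later gains have no concurrent control. Record and report the workshop date.
3. Add a sensitivity analysis that replaces the single on/off term by categories of time since the start of phase 3, for example 0-3, 3-6, 6-12 and >12 months. Report the time-averaged effect beside the constant-effect estimate.

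The cost is one sentence, one date and one extra model fit, using the districts' go-live dates. The averaged effect has a standard error about 25-60% larger and does not recover a workshop gain made on one calendar date, so it supplements the primary estimate and does not replace it. Because the article reports enrolment complete and analysis under way, the addition should be dated and labelled as such.

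### For mRS cut-offs other than 0-2 the plan names only an undefined area under the curve, which on neither per-cut-off reading gives an adjusted effect of the strategy

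*Protocol article*

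**What the plan says.** The Statistical Analysis section of the protocol article sets out the main model: "We will use a generalized linear mixed model following the basic model proposed by Hussey and Hughes [26], including the 6 districts as clusters". To guard against bias from changes over calendar time, the authors will stratify by the two stroke centers and "add a fixed effect for the secular trend stratified by each of these 2 hospitals, taking into account the control variables". The section on control variables lists them: "Control variables were age, sex, pre-mRS score, and severity of stroke", the last measured by the NIHSS at admission. The mRS is to be analysed as an ordinal scale.

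One cut-off is fixed in advance under Secondary Outcomes, the "dichotomization of the mRS (day 90) into scores of 0-2 and 3-6", and Statistical Analysis takes up the same split again. For other cut-offs the article offers one sentence: "the area under the curve for different mRS cutoff values will be calculated in an exploratory sensitivity analysis". It does not name the curve, the predictor or the outcome variable of that AUC.

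Under Power Considerations the authors give up a superiority test and say they will instead "explore the clinical significance of the intervention effects".

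**The concern.** Once testing is set aside, estimated effects are the trial's main product. An analysis over several cut-offs would be expected to return an effect at each one, on the same adjusted footing as the main analysis. An AUC is by origin a measure of discrimination. Depending on what is put into it, it may say almost nothing about the strategy, or it may restate a crude comparison of phases.

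The crude comparison is a particular problem in a stepped-wedge design, where intervention time falls later than control time by construction. What is at stake is a secondary matter: whether the reader can see how the adjusted benefit is spread over the scale, and whether one common odds ratio summarises it fairly.

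**Working it through.** The article gives no figure for this AUC, so there is nothing to reproduce. The sample size of 664 is unrelated. The check takes each possible meaning in turn. All outcome rates, prognostic strengths and trends below are assumptions, because the article gives none.

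**Reading A: discrimination of the covariate-adjusted model at each cut-off.** Simulated data had 400,000 patients, 1:1 allocation, one standard-normal prognostic score X standing in for age, pre-mRS and NIHSS, and logit P(good outcome) = −0.4 + log(OR) × phase + g × X. The AUC is that of the full linear predictor.

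| True OR | AUC, g = 1.0 | AUC, g = 1.5 |
|---|---|---|
| 1.0 | 0.740 | 0.813 |
| 1.5 | 0.743 | 0.814 |
| 2.0 | 0.749 | 0.817 |
| 0.5 | 0.751 | 0.819 |

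Changing the prognostic strength from 1.0 to 1.5 moves the AUC by about 0.07 (0.813 − 0.740 = 0.073). Going from no effect to an odds ratio of 2 moves it by 0.009 at g = 1.0 and 0.004 at g = 1.5. A doubling and a halving of the odds differ by 0.002 in both columns.

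Over all six cut-offs of a proportional-odds scale (g = 1.2), the AUC ran from 0.772 to 0.782 with no effect and from 0.774 to 0.782 with a common odds ratio of 1.5.

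**Reading B: phase against the dichotomised mRS.** With phase as classifier of outcome,

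AUC = 0.5 + [P(intervention | good) − P(intervention | poor)] / 2.

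For equal groups with 40% good outcome in control and 50% under intervention, P(intervention | good) = 0.50/0.90 = 0.5556 and P(intervention | poor) = 0.50/1.10 = 0.4545. The AUC is 0.5 + 0.1010/2 = 0.5505. Intervention rates of 40%, 45% and 60% give 0.500, 0.526 and 0.600.

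With the dichotomised mRS as classifier of phase, the AUC is exactly 0.5 + (risk difference)/2, so a 10-point difference gives 0.550. Either way the AUC follows size and direction, but it is a rescaled crude contrast.

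To see what the missing trend adjustment can do, take the phase lengths in the Study Design section: control 3 to 15 months and intervention 14 to 26 months, so 3 + 26 = 15 + 14 = 29 months per cluster. Assume six equally spaced steps from month 3 to month 15, equal accrual, no implementation gap, a 40% starting rate of mRS 0-2, and phase as classifier of outcome.

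| Trend in log-odds per month | Rate at month 29 | True OR | AUC |
|---|---|---|---|
| 0 | 40% (control) | 1.5 | 0.543 |
| 0.01 | 47% | 1.0 | 0.514 |
| 0.02 | 54% | 1.0 | 0.528 |
| 0.03 | 61% | 1.0 | 0.542 |

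The last row is a strong trend, chosen to show where it equals an odds ratio of 1.5. The weaker trends give part of that shift.

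**Reading C: Mann-Whitney AUC over the whole scale.** This is a real effect measure (0.500 at odds ratio 1.0 and 0.553 at 1.5 in the proportional-odds simulation). It is one number for the whole scale, however, not one per cut-off.

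**The case against.** A reader might infer that the AUC cannot show whether the result depends on the cut-off, or that benefit at one end of the scale with harm at the other would stay hidden. The document does not support that. On Reading B, benefit at mRS 0-2 would put the AUC above 0.5 at that cut-off, and more patients at mRS 5-6 would put it below 0.5 at the 0-4 cut-off. The pattern would be visible, though unadjusted.

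The article also never says that the aim is to test robustness to the cut-off. That aim is inferred from the label of sensitivity analysis. The wording might even stretch to a single ROC curve traced by the mRS cut-offs, which is Reading C.

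Further, the article condenses a fuller plan that is not shown and may define the AUC. The missing definition alone is therefore no fault. The analysis is both exploratory and a sensitivity analysis, in a study that forgoes testing. The main analysis is ordinal, the 0-2 split is a separate secondary outcome, and no stated decision rests on the AUC.

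All of this stands, and it limits the point. It does not remove it: the choice of statistic is stated in the article, and a definition would only settle which reading applies. Reading A says almost nothing about the strategy. Reading B drops the cluster, trend and covariate terms that the same section builds into the model.

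**Conclusion.** The point holds in a limited form. For cut-offs other than mRS 0-2 the article plans only an AUC, and neither per-cut-off reading supplies an adjusted intervention effect. As model discrimination, the AUC moved by about 0.01 or less between no effect and an odds ratio of 2 or 0.5 in the table above. As phase against dichotomised mRS, it is informative about the crude contrast but open to confounding by calendar time.

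The sizes rest on assumed prognostic strength, outcome rates and trends. The qualitative result for Reading A rests on the control variables being strongly prognostic. The result for Reading B rests on a trend existing, which the article treats as a possible source of bias.

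The importance is minor to moderate. The primary ordinal analysis and the prespecified 0-2 comparison are unaffected.

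**What to change.** In the Statistical Analysis section, replace the AUC by the adjusted intervention effect with its 95% interval at each cut-off (mRS 0-1, 0-2, 0-3, 0-4, and death). Estimate it from the same mixed model as the main analysis, with district, hospital-specific trend and control variables, and set it beside the common odds ratio of the ordinal model. This also shows whether the common odds ratio is a fair summary of the scale.

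If the AUC is kept, state its predictor, its outcome variable and the question it answers, and do not present it as evidence that the effect is robust to the cut-off.

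The cost is a change of wording and a few more fits on data already held. Intervals at the extreme cut-offs will be wide, and the report should say so.
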